### Adverse event reporting and management

2.9

All adverse events related to the administration of oxygen for OE MRI and [^18^F]MISO for the PET imaging procedures will be reported to the Trial Management Committee and reviewed as to requirement for reporting to the institution ethics review board. Determination of the severity of adverse events will be consistent with Common Terminology Criteria for Adverse Events (version 5). The relationship between an adverse event and the investigational product will be determined by the Investigator. An event should be considered related to treatment if, in the clinical principal investigator’s medical judgment, there is a reasonable possibility that the event may have been caused by the study drug. The investigator will be responsible for ensuring that any adverse events observed by the investigator or reported by the subject are recorded in the subject’s medical record and reported.

Scans will be stopped if suspected adverse drug reactions, changes in vital signs, electrocardiogram, or clinical laboratory results are observed and these changes pose a significant health risk. Clinically or medically significant suspected adverse drug reactions, and serious adverse events considered to be related to study procedures will be followed until resolved or considered stable. Subjects withdrawn from the study will be treated as deemed appropriate by the treating physician. Safety follow-up procedures will be performed and the appropriate Clinical Research Facilities will be completed.

### Statistical analysis

2.10

The sample size required for this study was calculated from a power analysis performed with the software GPower v.3.1. based on the hypothesis linked to the primary objective of the study. The hypothesis is that OE and BOLD MRI measurements of hypoxia within the tumour lesion will positively correlate (Pearson correlation coefficient > 0.7) to [^18^F]MISO values of uptake. The statistical test used in the power analysis was a correlation test using a point biserial model. Based on a Pearson correlation coefficient of 0.7, which was previously reported for the correlation of MRI measurements of hypoxia and the gold-standard immunohistochemical marker of hypoxia pimonidazole (27), the minimum sample size required to answer the hypothesis with 98% power and 5% two-tailed alpha, is 19. As such, up to 20 patients will be recruited for this study. A sample size of N=20 patients, which is large compared to the usual sample size used to estimate repeatability of ROI-averaged quantitative imaging measures (46), will allow us to test the hypothesis linked to secondary objective 1 - involving assessing the repeatability of OE/BOLD MRI measurements of hypoxia with the test-retest scan - with a specificity of at least 85% with 95% certainty (47); and the hypothesis linked to secondary objective 2 – involving the assessment of whether dose-painting radiotherapy plans result in improved TCP by more than 15% over conventional treatment - with 99% power and 5% one-tailed alpha (calculated with GPower v.3.1.).

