#### Primary objective

2.3.1

Spatial correlation between hypoxic tumour volume (HTV) determined with MRI and [^18^F]MISO will be evaluated via measurements of Dice similarity coefficient. Dice similarity coefficients > 0.75 will be considered a good spatial correlation. Quantitative correlation of voxel-wise and HTV-average levels of hypoxia will be evaluated via measurement of the Pearson’s correlation coefficient. Correlation coefficients > 0.7 will be considered a strong correlation (27).

#### Secondary objective 1

2.3.2

Repeatability of voxel-wise and HTV-average levels of hypoxia in the tumour, calculated as explained below for each hypoxia imaging biomarker, will be assessed via measurements of intraclass correlation coefficient (ICC). Repeatability is considered excellent, good, moderate or poor for ICC values > 0.9, 0.75-0.9, 0.5- 0.75 and< 0.5, respectively. Additionally, similarity between the HTV defined with the MRI biomarker at the two timepoints will be assessed via calculation of Dice similarity coefficient. Dice similarity coefficients > 0.9 will be considered a strong correlation.

#### Secondary objective 2

2.3.3

The predicted patient benefits of the hypoxia-guided dose-painting radiotherapy plan will be compared with the actual patient outcomes following conventional treatment, by using metrics including modelled tumour control probability (TCP) and toxicity measurement to organs at risks and healthy brain (including equivalent uniform dose). Voxel-wise dose-painting prescriptions within the conventional radiotherapy targets will be escalated from 60 Gy based on the level of hypoxia determined by the selected MRI imaging biomarker according to the method previously described by Toma-Dasu et al. (28). Targets delineation and constraints to organs at risk as per ESTRO-EANO guidelines (29) will be set equally for the optimisation of the conventional and dose-painting plans. Success for this objective will be achieved if the dose-painting plans result in improved TCP by more than 15% over conventional treatment, while dose metrics to organs at risk remain similar.

#### Secondary objective 3

2.3.4

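### The 98% power at n=19 comes from a point-biserial test of zero correlation; for two continuous measures it is about 95%, and it does not bear on the stated hypothesis of r > 0.7

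*Protocol article*

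**What the plan says.** Section 2.10 (Statistical analysis) ties the sample size to the primary hypothesis, which it words as MRI measurements that "will positively correlate (Pearson correlation coefficient > 0.7) to [^18^F]MISO values of uptake". The model is named: "The statistical test used in the power analysis was a correlation test using a point biserial model". The effect size is the same number as the threshold: "Based on a Pearson correlation coefficient of 0.7, which was previously reported for the correlation of MRI measurements of hypoxia". The result is that "the minimum sample size required to answer the hypothesis with 98% power and 5% two-tailed alpha, is 19", followed by "As such, up to 20 patients will be recruited for this study". The null value is not stated.

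Two other places describe the same objective. Section 2.3.1 (Primary objective) sets out the analysis: "Quantitative correlation of voxel-wise and HTV-average levels of hypoxia will be evaluated via measurement of the" Pearson coefficient, and "Correlation coefficients > 0.7 will be considered a strong correlation". Section 2.2 (Study hypotheses) states the primary hypothesis as a direct correlation between the MRI and PET measurements and gives no threshold.

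**The concern.** Section 2.10 does not match the planned analysis in two respects.

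- **Model.** A point-biserial correlation relates a binary variable to a continuous one. The planned analysis is Pearson's r between two continuous quantities, so the stated power belongs to another model.
- **Hypothesis.** The power is said to answer a hypothesis of r > 0.7, yet 0.7 is also the assumed true value. No test of that hypothesis could have 98% power when the truth lies on its boundary. The 98% must therefore belong to a test of something else.

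The stake is interpretation. A reader of this validation study may take an r above or below 0.7 as a verdict backed by 98% power, which the calculation does not provide.

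**Working it through.** **Inputs** (all from section 2.10): assumed correlation ρ = 0.7, two-sided α = 5%, stated power 98%, minimum n = 19, up to 20 recruited. The null ρ = 0 is inferred.

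**1. Reproduce the plan's figure.** For the point-biserial model, power comes from a noncentral t distribution with n − 2 degrees of freedom and noncentrality √[nρ²/(1 − ρ²)]. At n = 19 this is √(19 × 0.49/0.51) = 4.27 on 17 df. Two-sided power is 97.4% at n = 18, 98.03% at n = 19 and 98.5% at n = 20. So 19 is the smallest n reaching 98%, as stated. The one-sided version gives 99.3% at n = 19 and does not fit.

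**2. Same test, two continuous measures.** Bivariate normal data were simulated with ρ = 0.7 and one pair per patient, testing ρ = 0 at two-sided 5% (1,000,000 data sets per n; 200,000 for n = 16).

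| n | Power against ρ = 0 |
|---|---|
| 16 | 90.0% |
| 19 | 94.6% |
| 20 | 95.6% |
| 23 | 97.7% |
| 24 | 98.1% |

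Cross-check at n = 19 by Fisher's z: atanh(0.7) × √16 − 1.96 = 0.867 × 4 − 1.96 = 1.51, giving 93.4%; with the small-sample bias term it is 94.4%.

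**3. What that test shows.** At n = 19 the two-sided critical value of t on 17 df is 2.110, so the critical r is 2.110/√(17 + 2.110²) = 0.456. A significant result therefore shows a non-zero correlation, not one above 0.7.

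**4. Chance that the observed r exceeds 0.7 when ρ = 0.7.** By simulation this is 53.4% at n = 19 and 53.3% at n = 20. Check at n = 20: the bias of Fisher's z is 0.7/(2 × 19) = 0.0184; multiplied by √17 it is 0.076, and Φ(0.076) = 53%. A larger sample does not help; at n = 24 the figure is still 53.0%. At n = 20 it is 70.5% for ρ = 0.75, 85.8% for ρ = 0.80 and 95.7% for ρ = 0.85.

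**5. If r > 0.7 had to be shown formally.** A one-sided 2.5% Fisher z test of ρ ≤ 0.7 at n = 20 rejects 3.0% of the time at ρ = 0.7 (its error rate), 17.6% at ρ = 0.8 and 74.4% at ρ = 0.9.

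**6. Precision.** With r = 0.7 and n = 20, Fisher's z gives 0.867 ± 1.96/√17 = 0.392 to 1.343, a 95% CI for r of 0.37 to 0.87.

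**The case against.** The calculation is disclosed (software, model, effect size, alpha, sidedness) and its arithmetic is right for the model named. The correct model still gives 95-96% at the planned size and about 90% with 16 pairs, and nothing in the article makes 98% a requirement. A test of zero correlation is also the natural test of the hypothesis in section 2.2. All of this stands. It makes the choice of model a minor matter and leaves the sample size alone. It does not rescue the sentence in section 2.10, which attaches 98% to a hypothesis of r > 0.7.

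Two stronger readings are tempting, and the documents do not support them.

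- **That the trial has a pass/fail rule which a biomarker with a true correlation of 0.7 would fail 47% of the time.** Section 2.3.1 only labels r > 0.7 as strong. Where the protocol means a success criterion it says so, as for secondary objective 2 in section 2.3.3; there is no such sentence for the primary objective.
- **That 20 patients leave too little margin over 19.** The article gives no dropout rate, section 2.6.1 makes a confirmed diagnosis an inclusion criterion, and replacement rules may be in the full protocol. Power also falls slowly below 19.

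**Conclusion.** The concern holds as an error of statement in section 2.10. The 98% is the power of a point-biserial test of zero correlation. For the planned Pearson analysis the power against zero is about 95% at n = 19 and 96% at n = 20, and 98% would need about 24 patients. The more material point is that on no reading is 98% the power for r > 0.7. With the protocol's own assumed value, an observed r above 0.7 has about a 53% chance, and a formal demonstration has only the test's error rate. Section 2.10 is also stricter than sections 2.2 and 2.3.1.

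The zero null is inferred from exact reproduction. The 95-96% and the 53% assume bivariate normality, one value per patient (such as the HTV average), a true correlation of 0.7 and a single comparison; the 53% also reads r > 0.7 as a statement about the point estimate. They do not apply to voxel-wise correlation within a patient. The primary objective covers two MRI methods and two timepoints, and each figure is for one of those comparisons.

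**What to change.** - Keep 20 patients.
- In section 2.10, replace the point-biserial statement with: about 95-96% power to reject ρ = 0 at ρ = 0.7, two-sided 5%, bivariate normal model, with 19-20 evaluable MRI/PET pairs (about 90% with 16). State the null value.
- Word the hypothesis there as in section 2.2: a non-zero correlation in the expected direction.
- Report r with its 95% confidence interval, and give the expected width (0.37 to 0.87 at r = 0.7, n = 20).
- Keep r > 0.7 in section 2.3.1 as a descriptive label, and say that the sample size is not powered to establish it.

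The cost is a few sentences and a slightly lower stated power. Under this wording an observed r of about 0.44 at n = 20 would be significant, which is a modest bar for validation, so the confidence interval should carry the interpretation. If the sponsor prefers to claim a correlation above 0.7, that needs its own sample size with an assumed true value above 0.7.

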## Discussion

3

This diagnostic/prognostic imaging study will enable validation of the role of non-invasive MRI biomarkers of hypoxia that could be used to improve diagnosis, radiation treatment, prognosis and treatment response assessment of GBM patients. This study is ambitious in that it aims to characterise the evolution of tumour hypoxia levels during the whole course of patient management pipeline, with a plan to acquire MRI and PET/CT scans pre-operatively at diagnosis, prior to commencement of chemoradiation treatment, 12 weeks following completion of radiotherapy and at suspected diagnosis of recurrence, and supplementary MRI scans in a test-retest setting prior to commencement of radiotherapy and during radiotherapy. The supplementary MRI scans, which are required to test hypothesis for secondary objectives 1 and 4, will be considered optional based on patients’ status and compliance. Similarly, patients will be invited for repeat OE/BOLD MRI and [^18^F]MISO PET/CT scans only in case of suspected recurrence on long term MRI surveillance, meaning that there might only be a subset of patients whose data will be used to test hypothesis of secondary objective 3. Nonetheless, this study will generate a large amount of longitudinal multimodal MRI and PET imaging data that will be extremely valuable to unveil important dynamic changes in tumour physiology that currently limit treatment efficacy, thereby providing a means to develop more effective, personalised treatment strategies.

It is worth mentioning that one potential limitation in our study design is the challenge of including a selection criterium to ensure that the cohort of patients enrolled in the study exhibits different levels of hypoxia. This is important to ensure a more robust evaluation of the correlation between the OE/BOLD MRI biomarkers of hypoxia and [^18^F]MISO uptake levels. However, achieving such patients selection prior to enrolment in the study is neither trivial nor feasible in our study, because it would require quantification of hypoxia tumour levels via [^18^F]MISO PET scan, which is not performed as a routine standard-of-care diagnostic scan at our clinical centre. We mitigated the risk of this potential limitation by considering the typical incidence of hypoxia levels in GBM tumours. We looked at the results of a previously published clinical study quantifying regional levels of hypoxia in newly diagnosed GBM patients with [^18^F]MISO PET (12). This study enrolled 22 patients who had varying hypoxic tumour volumes (range: 0.1-129.3 cm^3^, median: 12.85 cm^3^) and heterogeneous levels of hypoxia (range T/B_max_: 1.2-4.2, median: 4.05). As we aim to recruit a similar number of patients with the same pathology, we assume to recruit a cohort of patients with similar hypoxia tumour volume/levels characteristics. It will certainly be important to report these metrics in our study results.

Moreover, we acknowledge that in our study we reserve the option of using either nasal prongs or a non-rebreather face mask for the delivery of oxygen gas in the OE MRI protocol. The choice for the oxygen delivery method will be linked to the feasibility of fitting the non-rebreather mask into the 64-channel MRI head coil that will be used in the study. The use of nasal prongs, which may be necessary for patients for whom a face mask would not fit comfortably into the head coil, could potentially limit the fractions of inspired oxygen (FiO_2_) to approximately 40%, hence resulting into a low OE MRI signal-to-noise ratio. We have mitigated this risk by testing our OE MRI protocol on a healthy volunteer who received oxygen delivery via nasal prongs. The ▵R_1_ measured in the nasal concha was 0.04 ± 0.04 s^-1^, which is comparable to the ▵R_1_ of 0.05 ± 0.02 s^-1^ observed in the same region of interest in healthy subjects in a similar OE MRI study using a non-rebreather oxygen mask (48). This result suggests that a similar hyper-oxygenation effect in the tissue could be achieved either by use of nasal prongs or non-rebreather face mask. Notably, validating that OE MRI can identify regions of tumour hypoxia by using nasal prongs for oxygen delivery would have higher impact in the widespread clinical translation of this method, as nasal prongs are safe, not limited by coil design or head shape, routinely used and widely available to all clinical centres.

## Ethics statement

All patients enrolled in the study are to provide written informed consent in accordance with institutional guidelines. Ethics approval for this study was obtained from the Northern Sydney Local Health District Human Research Ethics Committee on 15 April 2022: registration number 2021/ETH11794. This covers all participating clinical sites, including the Royal North Shore Hospital (RNSH) and North Shore Radiology (NSR).
